## Abstract

**Background:**

Mental fatigue has been observed to increase early and accumulate during fencing competition days. Traditional warm-up structures in fencing, including coach-led one-on-one combat (TC), always require a physical sparring partner. Virtual reality combat (VC) can engage athletes in an immersive, entertaining sports environment with specific motor-cognitive stimuli to enhance training and mental preparation, which may facilitate a quality warm-up.

**Aims:**

This study will compare the effects of VC with those of TC in the specialized warm-up section, on fencing-specific performance and fencers' fatigue levels.

**Methods:**

This study will be a within-subjects, randomized crossover design. It has been ethically approved and registered. Informed consent will be obtained from all participants. Twenty Epee fencers will be recruited and matched for gender and fencing level. The fencers' pair will be randomly assigned in a counterbalanced order to commence the experimental condition with VC or the control condition with TC first. Standardized measures of mental and physical fatigue, and motor-cognitive performance will be conducted pre- and post-warm-ups.

**Analysis:**

Linear mixed-effects models will be used for time, condition, and their interaction effects. Other subjective perceptions after VC/TC and heart rate responses to VC/TC will be collected and compared between conditions via paired samples t-tests.

**Discussion:**

This is the first time the virtual reality technology will be integrated into a traditional fencing warm-up to explore the feasibility of virtual combat as an on-field alternative. The practice-oriented study seeks to inform pre-competition warm-up structures, management of mental fatigue, and subsequent performance enhancement in real-world combat sports.

KEY POINTS:What the study is likely to add/Possible implications:
•By assessing subjective and objective indicators of mental and physical fatigue, and an ecologically valid fencing-specific test, this study will scientifically verify the effects of a traditional warm-up structure on subsequent performance and fencers' fatigue level.•For the first time, the study will explore a fencing-themed virtual combat being integrated into a traditional fencing warm-up procedure as a feasible, on-field alternative.•Applying a brief virtual reality exergame before competition can engage athletes in an entertaining scenario that provides specific motor-cognitive stimuli, which may buffer fatigue perception and facilitate mental preparation.•The practice-oriented study may inform redesign of warm-up structures, management of mental fatigue, and subsequent performance enhancement in real-world combat sports.

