## Introduction

1

Fencing is an open-skilled combat sport characterized by high intermittency [1], with short bursts of sword fighting and frequent rest intervals [2]. This leads to non-maximal physiological demands and relatively minor physical fatigue [3]. Fencing, however, requires the allocation of mental resources and perceptual-cognitive skills (e.g., sustained attention, information processing, response inhibition) for performance maintenance and success [[4], [5], [6]]. The prolonged interaction between motor and cognitive demands in the congested competition format (i.e., featuring consecutive preliminary and elimination bouts on the same day) can cause the onset of mental fatigue in fencers [7,8]. Longitudinal tracking during a national championship revealed elevated perceived mental fatigue and slower reaction time (RT) after competitions, suggesting a detrimental effect of mental fatigue on fencing performance [8]. During the period, the daily baseline mental fatigue fluctuated and peaked on competition days [8]. Furthermore, in the early stage of the consecutive bout progression, mental fatigue tended to accumulate faster [8]. This highlights the importance of mental fatigue management since the competition mornings [9]. The pre-competition preparation period, which may first determine the initial state of mental fatigue and subsequent competitive performance, emerges as a valuable time window worthy of attention.

Pre-competition warm-up is vital to attain optimal performance by evoking temperature, metabolic, neural, and psychological-related effects [10]. Meanwhile, warm-up strategies across sports are developed largely through a trial-and-error basis and the coach's experience [10]. Typically, a pre-competition warm-up protocol in fencing includes a generalized physical section, and the coach or sparring partner-led, technical/tactical drills and combat in a specialized section that requires a 1:1 personnel configuration to meet its high-level, competition-like demands. Yet, scientific evidence is lacking regarding the effect of such a warm-up on subsequent fencing performance. Moreover, mental fatigue could arguably build up due to the specific motor-cognitive demands from the warm-up combat, exacerbating its accumulation throughout the forthcoming competition day [9]. Further optimization of the warm-up could potentially enhance the performance [11,12] but lower the risk of prematurely elevating mental fatigue in fencers.

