Importantly, VR is reported to consistently stimulate the autonomic nervous system, as evidenced by increases in heart rate (HR) and skin resistance [19]. It can also lead to reduced vagal activity in the parasympathetic system, as shown by lower HR variability [20], indicating a similar mental fatigue state [21]. Research further suggests that engaging with immersive virtual content increases cognitive demand, potentially causing cognitive decline due to the user's limited attentional resource [22]. Despite being a promising technology that engages the specific motor-cognitive processes that are critical for fencing warm-up and competition-related performance, key concerns remain. It is not yet explored to what extent on-field VR combat can prime the real-world performance, nor what the potential effects are on mental fatigue in fencers. Consequently, this study will compare the effects of virtual combat (using VR) with those of traditional warm-up combat in the specialized warm-up section, on fencing-specific performance and fencers' fatigue levels. This study seeks to inform practitioners to evaluate and optimise warm-up practices. It is particularly relevant when access to an appropriate competitive sparring partner may be limited by availability, or an adapted preparation is required in official competitions, in consideration of the fencer's initial fatigue state.

*Aims*. The primary aim is to compare the acute effects of a 10-min VR combat with a 10-min traditional one-on-one combat during the 20-min specialized warm-up section, on subsequent fencing-specific psychomotor performance and subjective mental and physical fatigue levels in fencers. The secondary aims are: (1) to explore the athlete's psychological experience of the task load, readiness, and enjoyment; (2) to explore the behavioral indicators of mental fatigue and physiological response in the two specialized warm-up conditions.

*Hypotheses*. The hypotheses are: (1) VR combat will benefit the fencing-specific psychomotor performance, while inducing less subjective physical and mental fatigue due to the entertaining game nature. (2) Fencers will perceive less task load in a similar HR response, but more readiness and enjoyment after the embedded VR combat than traditional one-on-one combat. (3) The behavioral indicators of mental fatigue will align with the subjective perceptions of fencers.

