### Procedures

2.4

Eligible fencers visit the club pistes 3 times at a fixed slot (e.g., weekly routine training session at 15:00–17:30 to improve adherence), including a familiarization and two conditions (EXP/CON). The washout period will be at least 48h between conditions. The EXP and CON will take approximately 50min. Upon arrival and after preparation, a 15-min standardized general warm-up will be organized by the physical coach before T0. Next, 10min technical drills will be provided by the head coach. In EXP, the two fencers will start VC on their own for 10min. In CON, the paired fencers will conduct TC in the same format for 10min. Immediately before and after the 20-min specialized warm-up (i.e., technical drills and VC/TC), standardized measurements at T0 and T2 will be performed as follows: a 1-min digital questionnaire to collect subjective perceptions, a brief psychomotor vigilance test (PVT-B) to evaluate the reaction performance for 3min, and an Epee fencing-specific test (FST) to assess the reaction speed and lunge attack accuracy of the random targets for another 3min. Between the technical drills and VC/TC (T1), the questionnaire will be prompted to the fencers. Participants will be equipped with HR chest bands (Firstbeat, Garmin, Finland) throughout conditions to check the physiological response to VC/TC.

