## Discussion

3

This study attempts to verify the previously documented advantages of VR technology[14,15] in a real-world competitive fencing context. The feasibility of VR will be explored to replace the human resources that a coach or sparring partner-led, competitive one-on-one combat requires during the pre-competition warm-up. We hypothesize that VR combat could serve as a warm-up for the subsequent fencing performance. Meanwhile, the brief VR combat is supposed to be flexible, self-organized, and entertaining to buffer fatigue perceptions [17].

This study design demonstrates strong novelty and practical relevance. First, the evidence supporting the redesign of the pre-competition warm-up is derived from empirical longitudinal monitoring data in official fencing competitions [8,9]. The VR application of the dual-task paradigm (combined physical and cognitive exercise) is promoted by positive findings from a 5-week brain endurance training intervention among fencers [18]. Furthermore, the structure, content, and timing of the warm-up session have been developed strictly based on empirical investigations in this fencing community. To the authors' knowledge, this is the first time VR will be integrated in a traditional fencing warm-up. By assessing subjective and objective indicators of mental fatigue and fencing-specific performance, this study will effectively bridge the gap between research and on-field fencing practice.

However, this study protocol is risked by several limitations that should be acknowledged. The acute effects of the intervention will not account for dose-related factors such as difficulty or duration of the VR utilization. Further research may be needed to optimize the dose and timing of the exergame. Moreover, the specialized warm-up will be evaluated using a skill test (i.e., FST) rather than in a real competition, which may limit the ecological validity of the findings [30]. Regardless, it provides a step towards a model for the assessment of performance. Despite these acknowledged constraints, the practice-oriented protocol will provide valuable insights into modulating pre-competition warm-up, managing mental fatigue, and enhancing fencing performance in a real-world context.

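### The Key points promise to verify the effect of the traditional warm-up, but the design identifies only the VR-versus-traditional contrast; the T0–T2 change within a condition is inseparable from time and repeat testing

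*Protocol article*

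**What the plan says.** The first key point in the Abstract promises that "this study will scientifically verify the effects of a traditional warm-up structure on subsequent performance", and likewise on fatigue. The Introduction prepares this as a gap to be filled: after describing the usual fencing warm-up as a general physical section followed by a specialized section, it says that "scientific evidence is lacking regarding the effect of such a warm-up on subsequent fencing performance".

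The stated aim is different and comparative: "The primary aim is to compare the acute effects of a 10-min VR combat with a 10-min traditional one-on-one combat". The sample size in Section 2.3 is likewise based on the time-by-condition interaction.

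The design (Sections 2.1 and 2.4) has two conditions, EXP with VR combat and CON with traditional combat. In both, "a 15-min standardized general warm-up will be organized by the physical coach before T0". Ten minutes of coach-led drills and ten minutes of combat follow, and then T2. The reaction test (PVT-B) and the fencing-specific test (FST) are done at T0 and repeated at T2. At T1, between drills and combat, only the questionnaire is given.

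On analysis, the Abstract says: "Linear mixed-effects models will be used for time, condition, and their interaction effects". Section 2.11 adds Bonferroni post-hoc tests where appropriate, and partial eta-squared for significant model effects. Section 2.9.2 says that RT and RAcc will be compared before and after the specialized section.

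**The concern.** To verify what a traditional warm-up does, one needs to know what would have happened over the same interval without it. No condition supplies that. What the plan does produce is a time main effect and, through post-hoc tests, a T0–T2 contrast within CON. Someone looking for support for the key point would turn to these, and Section 2.11 provides for testing them and giving the significant effects an effect size.

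Suppose both conditions improve from T0 to T2 and the interaction is null. That result is compatible with two effective warm-ups. It is equally compatible with two ineffective ones plus a gain from taking the tests a second time. The data could not tell these apart, so a headline contribution would rest on a quantity that the design does not identify.

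**Working it through.** **1. The plan's own figure.** Section 2.3 gives partial eta-squared 0.12, α = 0.05, power 0.90, correlation 0.5, ε = 1 and a minimum N of 15.
- f = √(0.12/0.88) = 0.369, as stated.
- With m = 4 repeated cells (2 conditions × 2 times), λ = f²·N·m/(1−ρ) = 0.369² × 15 × 4/0.5 = 16.3, with 3 and 14 × 3 = 42 degrees of freedom. Power is 0.915 at N = 15 and 0.977 at N = 20.
- The figure of 15 reproduces. For dropout, 15/(1−0.15) = 17.6, so 18 would be enough; 20 are planned.

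This shows where 15 comes from. Whether a four-level layout suits an interaction with one degree of freedom is a separate question and is not used here. The present point changes no sample size.

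**2. What each contrast estimates.** For a performance outcome, let D be the effect of the drills, C_TC and C_VC the effects of the two forms of combat, and δ everything else between T0 and T2: elapsed time, carry-over or fatigue from the T0 tests, and retest practice.
- CON change: D + C_TC + δ
- EXP change: D + C_VC + δ
- Time main effect: D + (C_TC + C_VC)/2 + δ
- Interaction: (D + C_VC + δ) − (D + C_TC + δ) = C_VC − C_TC

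Only the interaction is free of δ, provided δ is the same in both conditions. The time main effect is not even the right target for the key point, because it mixes VR and traditional combat. The CON change is the right target, but it contains δ in full.

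**3. Aliasing.** The fixed-effect matrix for the four cells (intercept, time, condition, interaction) has rank 4. Adding a column for a practice or time shift at T2 leaves the rank at 4, so no analysis of these data can estimate δ separately.

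**4. δ is not obviously negligible.** By Section 2.9.3, one FST is 10 trials of three shuttles and a lunge. The T0 test alone adds 10 × 3 = 30 shuttles and 10 target lunges of fencing-specific activity shortly before the drills.

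**5. Illustration.** Assumptions: no true effect of drills or either combat (D = C_TC = C_VC = 0), N = 20, total SD 1, ρ = 0.5, paired tests on change scores, 20,000 runs. The SD of a T0–T2 change is √(2 × (1−0.5)) = 1, so a shift s moves the CON test statistic by about s√20.

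| Assumed shift δ (SD) | s√20 | CON T0–T2 test, p < 0.05 | Interaction test, p < 0.05 |
|---|---|---|---|
| 0 | 0 | 5% | 5% |
| 0.2 | 0.89 | 14% | 5% |
| 0.4 | 1.79 | 39% | 5% |
| 0.6 | 2.68 | 72% | 5% |

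The mean interaction estimate stayed at zero to within 0.004 SD throughout. The shifts are assumptions; the documents give none.

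**The case against.** The strongest reply is that every operative part of the protocol is comparative. The aims and the sample size concern VR against traditional combat, and the sentence at issue sits in a list of likely contributions. This stands, and it limits the point. A reader might infer that the main analysis is invalid; the documents do not support that, because the shared drift cancels in the interaction and order is counterbalanced. The reply does not dispose of the point, since the plan also tests time, allows post-hoc contrasts and describes a before-and-after comparison.

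Section 2.6 provides a familiarization visit with the whole test battery, feedback and extra repeats if needed. This may well reduce retest practice. It does not remove within-session time or the effects of the T0 tests, and nothing measures what remains.

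T1 separates drills from combat for MVAS and RPE, and skill practice is an unlikely explanation for a fatigue rating. Both are fair. T1 does not help RT, RAcc, LT or LAcc, however, and for the two ratings the T1–T2 change still has no control for elapsed time.

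The pre/post window is openly the 20-minute specialized section, so the lack of a measurement before the general warm-up is no fault in itself. It matters only because the key point speaks of the traditional warm-up structure, of which the general section is a part.

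A reader might also count the Discussion sentence "We hypothesize that VR combat could serve as a warm-up for the subsequent fencing performance" as a second overclaim. It is worded as a hypothesis and need not change. Nor does any passage say that a null interaction would be reported as proof that both warm-ups work; that is a risk the wording leaves open, not a stated rule.

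Finally, declaring some model terms descriptive could be left to a fuller analysis plan. But the claim is made in this article, so the limit on it belongs here too.

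**Conclusion.** The point holds as one about interpretation. With two active conditions and T0 always before T2, the CON T0–T2 change and the time main effect are fully aliased with elapsed time, prior testing and residual practice, and the general warm-up is not evaluated at all. The key point therefore promises more than the design can deliver.

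How much this would mislead depends on a shift that the documents do not quantify. Over the assumed range of 0 to 0.6 SD, the chance of a significant CON change with no warm-up effect runs from 5% to 72%. The primary comparison of VR with traditional combat is unaffected, on the assumption that drift is equal in the two conditions, which counterbalancing supports with respect to order. The correction is worth making before data are seen, but it does not put the main analysis in doubt.

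**What to change.** Two changes of wording:
- In the Key points, replace the promise to verify the effects of the traditional warm-up with a statement that the study compares VR combat with traditional combat as part of the specialized warm-up, for performance and fatigue.
- In Section 2.11, add that the time main effect and the within-condition T0–T2 contrasts are descriptive and will not be interpreted as the effect of either warm-up.

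No extra condition, visit or participant is needed. The cost is a slightly narrower claimed contribution: the gap named in the Introduction, the effect of the traditional warm-up itself, stays open after this study.

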## Introduction

1

Fencing is an open-skilled combat sport characterized by high intermittency [1], with short bursts of sword fighting and frequent rest intervals [2]. This leads to non-maximal physiological demands and relatively minor physical fatigue [3]. Fencing, however, requires the allocation of mental resources and perceptual-cognitive skills (e.g., sustained attention, information processing, response inhibition) for performance maintenance and success [[4], [5], [6]]. The prolonged interaction between motor and cognitive demands in the congested competition format (i.e., featuring consecutive preliminary and elimination bouts on the same day) can cause the onset of mental fatigue in fencers [7,8]. Longitudinal tracking during a national championship revealed elevated perceived mental fatigue and slower reaction time (RT) after competitions, suggesting a detrimental effect of mental fatigue on fencing performance [8]. During the period, the daily baseline mental fatigue fluctuated and peaked on competition days [8]. Furthermore, in the early stage of the consecutive bout progression, mental fatigue tended to accumulate faster [8]. This highlights the importance of mental fatigue management since the competition mornings [9]. The pre-competition preparation period, which may first determine the initial state of mental fatigue and subsequent competitive performance, emerges as a valuable time window worthy of attention.

Pre-competition warm-up is vital to attain optimal performance by evoking temperature, metabolic, neural, and psychological-related effects [10]. Meanwhile, warm-up strategies across sports are developed largely through a trial-and-error basis and the coach's experience [10]. Typically, a pre-competition warm-up protocol in fencing includes a generalized physical section, and the coach or sparring partner-led, technical/tactical drills and combat in a specialized section that requires a 1:1 personnel configuration to meet its high-level, competition-like demands. Yet, scientific evidence is lacking regarding the effect of such a warm-up on subsequent fencing performance. Moreover, mental fatigue could arguably build up due to the specific motor-cognitive demands from the warm-up combat, exacerbating its accumulation throughout the forthcoming competition day [9]. Further optimization of the warm-up could potentially enhance the performance [11,12] but lower the risk of prematurely elevating mental fatigue in fencers.

From this perspective, Virtual Reality (VR) technology holds potential as a controlled and adaptable warm-up tool, enabling the simulation of sport-specific perceptual and decision-making demands while limiting unnecessary physical and cognitive load. Indeed, VR is already recognized as a valuable tool in sports performance contexts, offering applications for training, skill learning, and mental preparation [13]. These applications include targeting sports-specific perceptual-cognitive skills [14]. It immerses users in realistic and interactive scenarios of varying complexity, usually via a head-mounted display and handheld controllers [15]. Recently, exergames have been developed to engage athletes in a virtual sports environment with entertaining tasks mimicking technical drills and even competition [16]. The acute effects of VR exergaming on cerebral activity and cognitive function are documented, for instance, the facilitation of selective attention and inhibitory processes [17]. Accordingly, fencing-themed VR exergames, which are designed for individuals' virtual combat against an avatar, may induce representative motor and cognitive demands concurrently when embedded into warm-ups. Moreover, the brain endurance training (i.e., intermixed physical and cognitive tasks) has been proven to improve performance in fencers [18]. Therefore, a similar benefit may be expected from VR exergaming warm-up, as it employs the same dual-task paradigm.

Importantly, VR is reported to consistently stimulate the autonomic nervous system, as evidenced by increases in heart rate (HR) and skin resistance [19]. It can also lead to reduced vagal activity in the parasympathetic system, as shown by lower HR variability [20], indicating a similar mental fatigue state [21]. Research further suggests that engaging with immersive virtual content increases cognitive demand, potentially causing cognitive decline due to the user's limited attentional resource [22]. Despite being a promising technology that engages the specific motor-cognitive processes that are critical for fencing warm-up and competition-related performance, key concerns remain. It is not yet explored to what extent on-field VR combat can prime the real-world performance, nor what the potential effects are on mental fatigue in fencers. Consequently, this study will compare the effects of virtual combat (using VR) with those of traditional warm-up combat in the specialized warm-up section, on fencing-specific performance and fencers' fatigue levels. This study seeks to inform practitioners to evaluate and optimise warm-up practices. It is particularly relevant when access to an appropriate competitive sparring partner may be limited by availability, or an adapted preparation is required in official competitions, in consideration of the fencer's initial fatigue state.

*Aims*. The primary aim is to compare the acute effects of a 10-min VR combat with a 10-min traditional one-on-one combat during the 20-min specialized warm-up section, on subsequent fencing-specific psychomotor performance and subjective mental and physical fatigue levels in fencers. The secondary aims are: (1) to explore the athlete's psychological experience of the task load, readiness, and enjoyment; (2) to explore the behavioral indicators of mental fatigue and physiological response in the two specialized warm-up conditions.

*Hypotheses*. The hypotheses are: (1) VR combat will benefit the fencing-specific psychomotor performance, while inducing less subjective physical and mental fatigue due to the entertaining game nature. (2) Fencers will perceive less task load in a similar HR response, but more readiness and enjoyment after the embedded VR combat than traditional one-on-one combat. (3) The behavioral indicators of mental fatigue will align with the subjective perceptions of fencers.

